### Extracting hand-speech movement data

We will use deep neural networks and other machine learning methods to develop and train two computer programs that will automatically detect, respectively, hand key points (e.g. finger and thumb tips) in the video data [43], and syllable features in audio recording (Fig. 1). A series of movement features will be extracted in a fixed window period, by (1) experts in hand movement (JA, KL, [name]) and speech-like movements (LG), and (2) deep-learning approach applied directly on processed video data, to analyse their associations with biomarker-defined measures of AD pathology. The processed video data can be the hand-only cropped video or displacement (between fingertip and thumb-tip) over time data extracted from the raw video. Thus, two approaches, expert guided and AI-based ‘deep-learning’, will extract discriminative hand-speech movement features as input data for the multivariable model. The main outcome will be a validated personal computer (laptop and desktop) version of the TapTalk that discriminates preclinical AD from normal ageing in cognitively healthy adults ≥ 50 years old with defined sensitivity and specificity.

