### Statistical analysis

We will use data from 350 of a sample of 500 participants to develop multivariable models that classify data according to risk of preclinical AD pathology. Data from the remaining 150 will determine the externally validated sensitivity/specificity of candidate models in detecting preclinical AD. Hand-speech movement data will be normalised. Participants with blood biomarker levels in the preclinical AD range (e.g., p-tau 181, or a combination of blood biomarkers) will be classified as ‘AD positive’. We will use penalised logistic regression to measure the associations between movement patterns and AD positivity. Covariates may include age, gender, apolipoprotein E ([APOE] a risk gene for AD analysed through blood sampling as part of the ISLAND Project), years of education, and handedness. As a secondary, more agnostic approach, we will use deep learning methods to discover features in movement and speech-like data that map to AD positivity.

We will use cross-validation to avoid overfitting by selecting penalty terms (type and amount of shrinkage applied to coefficients) which optimise the bias-variance trade-off. Bootstrap procedures will be used to estimate model uncertainty. We will externally validate models using data from the remaining 150 participants. Receiver Operating Characteristic (ROC) curves will be plotted against the positive AD cut-off to assess the sensitivity/specificity of movement and speech-like models to discriminate the preclinical AD stage from normal ageing. The model with the highest area under the ROC curve (AUC) will be chosen as the TapTalk algorithm.

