### Sample size justification

The precise combination of blood-based biomarkers used to determine ‘positive’ preclinical AD pathology is yet to be determined as the scientific literature is developing quickly and new biomarkers are being developed regularly. We will review the literature before deciding on the best biomarker test, or combination of tests, that should be used to define AD pathology risk most accurately.

Currently p-tau 181 is considered one of the most accurate blood-based biomarkers for preclinical AD risk and we have therefore based our sample size calculation on this biomarker. As new tests are developed and are likely to be even more sensitive/specific than p-tau 181, the current calculation is a conservative estimate. We estimate that 17% of cognitively normal adults within our cohort have p-tau 181 in the preclinical AD range [55]. There are no tests of DDK compared to AD biomarkers, so we have based all calculations on finger tapping data.

We have performed ROC curve analysis using open data from Mollica et al. to calculate sensitivity and specificity of finger tapping speed and variability to predict CSF p-tau 181 [20]. This showed area under ROC curve (AUC) of 0.75 for a null linear model including age, gender and years of education, but not finger tapping. We calculated that the sample size to compare a screening test with an AUC > 0.90 against the null model requires 60 preclinical AD cases (positive p-tau181) and 290 healthy ageing controls (negative p-tau181). Thus, we will use 350 in the development dataset (expected 60 [17%] preclinical AD cases) and 150 in the validation dataset (expected 25 [17%] preclinical AD cases) to test cut-offs from the development model. The PROBAST tool [56] for assessment of prediction and diagnostic method studies confirms these development and validation strategies have a low risk of bias.

### AIM 2

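### Aim 1: cross-validation is described for the penalty only, and nothing extends it to the deep-learned, label-guided features that enter the same model

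*Protocol article*

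**What the plan says.** The relevant statements are spread over several sections of the protocol article.

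- **Extracting hand-speech movement data.** An expert-guided route and a deep-learning route "will extract discriminative hand-speech movement features as input data for the multivariable model". The section gives the purpose of extraction as relating the features to biomarker-defined AD pathology.
- **Statistical analysis (Aim 1), method.** Penalised logistic regression is the main method. As a secondary route, "we will use deep learning methods to discover features in movement and speech-like data that map to AD positivity".
- **Statistical analysis (Aim 1), overfitting.** "We will use cross-validation to avoid overfitting by selecting penalty terms (type and amount of shrinkage applied to coefficients". No other step is named as coming under cross-validation. "Bootstrap procedures will be used to estimate model uncertainty", but the text does not say which steps each bootstrap sample repeats.
- **Statistical analysis (Aim 1), split and model choice.** "We will use data from 350 of a sample of 500 participants to develop multivariable models", and "We will externally validate models using data from the remaining 150 participants". Then: "The model with the highest area under the ROC curve (AUC) will be chosen as the TapTalk algorithm". The text does not say on which data that AUC is judged.
- **Sample size justification (Aim 1).** About 60 positives are expected in the development set and 25 in the validation set. PROBAST is said to be the tool that "confirms these development and validation strategies have a low risk of bias".
- **Hand movement data collection, and Design (Aim 2).** Aim 1 findings decide which three to five tasks go into the smartphone version used in Aims 2 and 3.

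**The concern.** Cross-validation estimates performance honestly only for the steps repeated without the held-out fold. If a feature extractor is trained towards AD positivity on all development participants and its output is then passed to a cross-validated penalised regression, each held-out fold has already shaped its own predictors through its labels. The regression then sees inputs that separate the classes better than they would in new people, and tuning the penalty cannot detect this.

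The label-trained extractor is also the most flexible part of the pipeline. The Discussion speaks of more than 10,000 data points as model input, against about 60 positives. The article defines the scope of its own safeguard, and that scope leaves this step out.

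Three things are at stake: the internal AUC, the weight given to learned features against expert features, and any ranking of tasks made on development data. The ranking carries through to Aims 2 and 3.

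**Working it through.** **1. The plan's own figures.** At 17% prevalence, 0.17 × 350 = 59.5 (stated 60) and 0.17 × 150 = 25.5 (stated 25); 60 + 290 = 350. These reproduce, and no stated figure is in dispute.

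**2. Which steps use the AD label, and which are covered.**

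| Step | Uses AD label? | Named as under cross-validation? |
|---|---|---|
| Networks detecting hand key points and syllables | No need for it | Not relevant |
| Deep learning of features related to AD positivity | Yes, on the natural reading | No |
| Choice of penalty type and amount | Yes | Yes |
| Choice of tasks for the smartphone | Yes (most discriminating) | No |
| Choice of final model by AUC | Yes | No dataset named |

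**3. Size with no true signal.** From the plan: 60/290 positives/negatives for development and 25/125 held out. Assumed: 1,000 pure-noise features. Feature learning is represented by keeping the 20 features with the largest |Σ(x − x̄)(y − ȳ)| / SD(x). Ridge logistic regression follows, with the penalty chosen from 1, 10, 100 and 1,000 by ten-fold cross-validated AUC. Means (SD) over 60 replicates:

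| Features chosen on | Cross-validated AUC | AUC in the 150 |
|---|---|---|
| All 350, outside the folds | 0.850 (0.020) | 0.503 (0.061) |
| Training part of each fold | 0.506 (0.081) | 0.501 (0.061) |
| All 500 (penalty fixed at 10) | not computed | 0.789 (0.046) |

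Optimism in the first row is 0.850 − 0.503 = 0.347. The third row shows what would follow if feature learning also used the 150; the article does not say that it does. This run does not show which way the penalty moves. The median chosen penalty was 100 outside the folds and 10 inside, and with pure noise the inside choice is close to arbitrary.

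**4. Size when expert features carry signal.** Ten expert features were combined with one score trained on the same labels, again with 60/290. The number and strength of the learned inputs are assumptions.

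- Five settings, 25 runs each, learning outside the folds: cross-validated AUC 0.81–0.99 against true AUC 0.52–0.76. Cross-fitting the score gave an honest AUC, and a better final model in four of the five settings (for example 0.68 against 0.52, and 0.79 against 0.76). The hold-out AUC stayed within about 0.02 of the truth.
- Separate runs, 40 per setting, learning outside the folds, compared with expert features alone:

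| Learned inputs | True AUC, combined | True AUC, expert only |
|---|---|---|
| All noise | 0.51–0.60 | 0.67 |
| 5 of 100 informative | 0.62 | 0.68 |
| 10 of 50 informative (each AUC 0.60) | 0.75 | 0.68 |
| 20 of 100 informative | 0.77 | 0.67 |
| 20 of 150 informative | 0.74 | 0.68 |

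Internal AUC was optimistic throughout. Whether the combined model beats expert features alone depends on the inputs.

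**The case against.** The strongest reply is that the article never says features are learned outside the folds. It says only that cross-validation selects the penalty, which is ordinary practice, and nesting is often left to a fuller protocol or analysis plan. The first part stands: a reader might infer that learning happens outside the loop, but the documents do not state it. It does not dispose of the point, because the article describes both the label-guided step and a safeguard that omits it, and then publishes a conclusion of low bias.

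The second reply is the hold-out. The 150 are set aside to determine sensitivity and specificity, and if untouched they would expose an overfitted model (0.50 against 0.85 above). This stands, and it rules out the reading that the plan has no working control on overfitting. A clean hold-out reveals a poor model, however; it does not repair the penalty, the feature weights or a task ranking already made.

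Third, deep learning is called secondary, and the networks that detect key points and syllables need no AD label. Both are true, but the extraction section still names deep-learned features as inputs to the multivariable model.

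Two further inferences are unsupported. One is that the 150 are contaminated. The extraction section does not limit itself to the 350, but no sentence says it uses all 500, and models are to be developed on 350. The other is that the chosen algorithm will be worse than expert features alone; the last table shows this reversing when enough learned inputs are informative.

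**Conclusion.** The point holds in a limited form. As described, the overfitting control covers the penalty and not the label-guided feature learning that feeds the same model. Run in that order, the internal AUC will be optimistic: by about 0.35 in the no-signal illustration, and 0.81–0.99 reported against 0.52–0.76 true in the settings with expert signal. The penalty would be chosen against the same inflated figure. The algorithm, and any task ranking made on development data, can be degraded as a result.

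The final sensitivity and specificity are not shown to be biased, provided the 150 stay out of feature learning and model choice. The article does not spell out that condition. The sizes rest on assumed numbers and strengths of inputs and on simple stand-ins for deep learning; they show the mechanism and direction and do not forecast this study's result. The sentence citing PROBAST is not refuted, but the procedure as written does not yet support it.

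**What to change.** In the extraction and Aim 1 Statistical analysis sections, state that:

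1. Every step that uses the AD label (deep-feature training, selection of features and tasks, choice of penalty) is confined to the 350 development participants and repeated within each cross-validation fold and each bootstrap sample. Alternatively, state that the deep extractor is trained without AD labels, so that only the penalised regression sees them.
2. The final model, judged by highest AUC, is chosen on development data before the 150 are used.

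In the Aim 1 Sample size justification, make the PROBAST statement conditional on these two points.

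The cost is more computing time, because the extractor is retrained in every resample, together with a few lines of text. Internal AUCs will look lower. No extra participants or data are needed.

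### As written, Aim 1 uses the same 150 hold-out participants to choose the TapTalk model and to report its accuracy, which biases AUC and sensitivity upward

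*Protocol article*

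**What the plan says.** All of this is in the protocol article, Methods, Aim 1.

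- **Development** (Statistical analysis): "We will use data from 350 of a sample of 500 participants to develop multivariable models".
- **Role of the hold-out** (same section): "Data from the remaining 150 will determine the externally validated sensitivity/specificity of candidate models in detecting preclinical AD". The next paragraph repeats it: "We will externally validate models using data from the remaining 150 participants".
- **ROC step**, directly after: "Receiver Operating Characteristic (ROC) curves will be plotted against the positive AD cut-off to assess the sensitivity/specificity of movement and speech-like models".
- **Selection rule**, directly after that: "The model with the highest area under the ROC curve (AUC) will be chosen as the TapTalk algorithm".
- **Cross-validation** has one stated job: "We will use cross-validation to avoid overfitting by selecting penalty terms". The bootstrap is assigned to model uncertainty.
- **A second model family** stands beside penalised logistic regression: "As a secondary, more agnostic approach, we will use deep learning methods".
- **Sample size justification** expects 25 cases among the 150 and says that these participants test cut-offs taken from the development model. It adds that the PROBAST tool "confirms these development and validation strategies have a low risk of bias".

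**The concern.** A hold-out sample gives an unbiased estimate of accuracy only for a model fixed before that sample was looked at. If several models are scored in it and the best scorer is kept, the winner's result contains its real performance plus whatever chance favoured it in those people. Reporting that result as the model's accuracy is optimistic on average.

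The affected figures are the main outcome of Aim 1, which the section on extracting movement data describes as a validated test with defined sensitivity and specificity. Later studies do not repair them. Study 2.3 carries the Study 1 algorithm forward but judges it against decline on CANTAB, and Aim 3 judges TapTalk against clinical diagnosis. Neither estimates accuracy against the blood biomarker again.

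A smaller, separate matter is the label. The 150 are part of the same 500 people in a single-site study, so the comparison is a split-sample validation rather than an external one.

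**Working it through.** **1. The plan's case counts.** With 17% biomarker-positive: 0.17 × 150 = 25.5 (stated 25) and 0.17 × 350 = 59.5 (stated 60). Both reproduce. The hold-out has about 25 cases and 125 controls.

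**2. Where the selection happens.** The order of the text is: develop in 350, tune penalties by cross-validation, validate the models in the 150, plot ROC curves, take the highest AUC. The only accuracy comparison between models described before the choice is the one in the 150. No nested step, third data set or correction for optimism is described.

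**3. How noisy one AUC is in 25 cases and 125 controls.** Hanley-McNeil: SE² = [A(1−A) + (n₁−1)(q₁−A²) + (n₀−1)(q₂−A²)] / (n₁n₀), with q₁ = A/(2−A) and q₂ = 2A²/(1+A).

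For A = 0.75, the plan's AUC for the null model: q₁ = 0.600, q₂ = 0.643, so SE² = (0.1875 + 24 × 0.0375 + 124 × 0.0804)/3125 = 0.00354 and SE = 0.060. The same formula gives 0.056 at 0.80 and 0.042 at 0.90. Differences of a few hundredths between candidates are within chance.

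**4. Hand check for two equally good models.** The expected excess of the better of two estimates is SE × √[(1−r)/π]. The correlation r is an assumption. At A = 0.75, r = 0.3 gives 0.060 × 0.472 = 0.028, and r = 0.8 gives 0.060 × 0.252 = 0.015.

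**5. Simulation.** Binormal scores, 25 cases and 125 controls, cut-off fixed beforehand, the model with the highest AUC in the 150 chosen and its accuracy read from the same 150. Assumed, because the protocol does not state them: number of candidates, common true AUC of 0.75 to 0.90, and score correlation of 0.3 to 0.8. Mean inflation:

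| Equally good candidates | AUC | Sensitivity | Specificity |
|---|---|---|---|
| 2 | +0.008 to +0.026 | +0.012 to +0.036 | +0.003 to +0.008 |
| 5 | +0.019 to +0.052 | +0.035 to +0.074 | +0.006 to +0.014 |
| 20 | +0.030 to +0.080 | +0.057 to +0.112 | +0.012 to +0.024 |

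The row for two candidates is close to the hand check. Specificity moves little because it rests on 125 people, not 25.

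**6. Unequal candidates.** Five models with true AUCs spread over 0.75 to 0.85: AUC +0.011 to +0.030, sensitivity +0.019 to +0.046. Spread over 0.65 to 0.90: AUC +0.001 to +0.008.

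**7. With the choice made outside the 150.** Five candidates, chosen in an independent draw of 60 cases and 290 controls (a stand-in for selection by cross-validation in the 350), then evaluated once in the 150: mean bias at most 0.002 in absolute value for AUC, sensitivity and specificity.

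**The case against.** The strongest reply is that the selection sentence names no data set. The Sample size justification speaks of the development model in the singular and gives the 150 the task of testing its cut-offs, which fits a model already fixed in the 350. This stands as a caveat: the plan does not expressly say that the choice is made in the 150. It does not remove the point. The Statistical analysis section sends candidate models, in the plural, to the 150, and places the choice directly after that step. If earlier locking was meant, the text should say so. Nor is this detail that an article merely leaves to a fuller document, since the rule and its place in the sequence are both stated.

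The second reply concerns size, and it largely stands. The text clearly supports at least two candidates; five or twenty are assumptions. Equal true AUCs are the unfavourable case, and the plan aims for an AUC above 0.90. A reader might infer that the choice would be mostly noise, citing for instance that the winner of 5 to 20 models with true AUC 0.75 exceeds 0.80 in roughly 35 to 70% of simulated runs. That needs its comparator: a single prespecified model does so in about 17% of runs. It also applies only to near-identical models.

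Third, a reader might infer that the cut-off is re-optimised in the 150 or that specificity is inflated as much as sensitivity. Neither is supported. Cut-offs come from development, so the bias arises from model choice alone, and it hardly touches specificity.

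Fourth, the tool's criteria are not in the documents, so they do not show that the low-risk-of-bias rating must be withdrawn outright. They show only that the present selection step does not support it.

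**Conclusion.** The point holds in limited form. On the natural reading of the Aim 1 analysis section, choosing the model and reporting its accuracy share the same 150 people, so the reported AUC and sensitivity are biased upward on average. The direction follows from the procedure. The size cannot be derived from the protocol: it depends on how many candidates reach the hold-out, how correlated they are and how far apart their true performance lies. The AUC effect runs from almost nothing with one dominant model, through one to three hundredths for two close models, to as much as 0.08 for twenty close ones. Sensitivity is affected more, since it rests on about 25 cases.

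The documents do not support the stronger conclusion that the headline accuracy will be badly wrong. They do show that the result, as planned, cannot be presented as an untouched or external validation.

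**What to change.** In the Aim 1 Statistical analysis section, state that:

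1. the choice between candidate models (type, features, covariates, penalty) is made within the 350 only, by nested cross-validation or bootstrap;
2. one model is then locked together with its development-set cut-off;
3. the locked model is evaluated once in the 150, and that is the primary accuracy result;
4. results of other candidates in the 150 are secondary and do not change the choice.

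Replace the external-validation wording with hold-out or split-sample validation. In the Sample size justification, do not rest the low-risk-of-bias statement on the present selection step; reassess it once the order above is written in.

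The cost is wording and order of analysis, with no extra participants. The reported AUC and sensitivity may be slightly less favourable. The change has to be made before the 150 are examined, because the hold-out cannot be made untouched afterwards.

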### Sample size justification

The precise combination of blood-based biomarkers used to determine ‘positive’ preclinical AD pathology is yet to be determined as the scientific literature is developing quickly and new biomarkers are being developed regularly. We will review the literature before deciding on the best biomarker test, or combination of tests, that should be used to define AD pathology risk most accurately.

Currently p-tau 181 is considered one of the most accurate blood-based biomarkers for preclinical AD risk and we have therefore based our sample size calculation on this biomarker. As new tests are developed and are likely to be even more sensitive/specific than p-tau 181, the current calculation is a conservative estimate. We estimate that 17% of cognitively normal adults within our cohort have p-tau 181 in the preclinical AD range [55]. There are no tests of DDK compared to AD biomarkers, so we have based all calculations on finger tapping data.

We have performed ROC curve analysis using open data from Mollica et al. to calculate sensitivity and specificity of finger tapping speed and variability to predict CSF p-tau 181 [20]. This showed area under ROC curve (AUC) of 0.75 for a null linear model including age, gender and years of education, but not finger tapping. We calculated that the sample size to compare a screening test with an AUC > 0.90 against the null model requires 60 preclinical AD cases (positive p-tau181) and 290 healthy ageing controls (negative p-tau181). Thus, we will use 350 in the development dataset (expected 60 [17%] preclinical AD cases) and 150 in the validation dataset (expected 25 [17%] preclinical AD cases) to test cut-offs from the development model. The PROBAST tool [56] for assessment of prediction and diagnostic method studies confirms these development and validation strategies have a low risk of bias.

### AIM 2

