‘In phase’ means that both hands move simultaneously through the finger tapping cycle, whereas ‘out of phase’ means that each hand moves through the finger tapping cycle in the opposite direction to the other hand (i.e., 180 degrees out of phase so one hand has the finger and thumb opposed while the other hand has the finger and thumb spread apart). The cognitive task will be counting backwards aloud from 100 and constitutes a ‘dual motor-cognitive test’ when performed at the same time as finger tapping [53, 54]. Each hand will therefore be tested separately, and together, at a comfortable pace and at maximal pace, allowing for a number of finger-tapping measures to be calculated including, but not limited to, frequency, rhythm, inaccuracies (i.e. the wrong digit tapped on the sequential tests), ‘motor reserve’, calculated as a ratio (the maximal pace parameter divided by comfortable pace parameters), bimanual ‘motor cost’, calculated as the finger tapping parameters of one hand divided by the finger tapping parameters of same hand when both hands tapped together and the ‘dual cognitive-motor cost’, calculated as the finger tapping parameters divided by the finger tapping parameters during the counting backwards aloud from 100 task.

We will shorten this finger tapping protocol to around three to five tasks, aiming for a test duration of 2 to 3 min, in the smartphone version of TapTalk that will be used in Aim 2 and Aim 3. The choice of which tasks will comprise the shortened protocol will be based on the findings from Aim 1. We have purposefully kept a wide array of tests in Study 1 to clarify which tests combine best together, and with the DDK data, to best discriminate biomarker-defined AD pathology.

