We have already recruited 1382 participants with a wide age range of 50–92 years, and a large amount of hand and speech-like movement data from TapTalk will be obtained through this study. This new database, probably the only one of its kind in the world, will be stored for future research use by University of Tasmania researchers and, with permission, for external researchers.

Potential risks of the study are acknowledged and strategies to mitigate these are discussed. There is a risk of inadequate recruitment, but we will mitigate this by recruiting existing participants in established research cohorts, namely the longitudinal cohorts of ISLAND Project and from the ISLAND Clinic where participants are primed to take part in research. There is a risk that TapTalk is not sufficiently accurate, but we have mitigated this by selecting component test items based on evidence of sensitivity to preclinical AD, combining multiple tests to amplify the multivariable model input data [> 10,000 data points], and electing well-established, transparent statistical modelling approaches that reveal the most discriminatory components of motor data, allowing further refinement.

We have devised a study protocol that plans to collect a sufficiently large dataset to employ multiple modelling methods, including feature-agnostic deep learning. A further risk is that participants lack a computer camera or smartphone to provide video-recorded hand movement data and audio speech-like data, or do not wish to do so; we have mitigated this risk by recruiting participants from studies that have online assessments already, offering the opportunity for participants to attend the clinical research centre in person if preferred, and providing two methods (video recorded and audio recorded data collection) within TapTalk.

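### Aim 1's 60/290 sizes a comparison of two ready-made scores, yet those 350 people are used to build the score; the held-out 150 fall short of that number, and the low-risk-of-bias claim is premature

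*Protocol article*

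**What the plan says.** All references are to the protocol article, Aim 1.

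- *Sample size justification*: the comparator has an "area under ROC curve (AUC) of 0.75 for a null linear model including age, gender and years of education, but not finger tapping". The target is the "sample size to compare a screening test with an AUC > 0.90 against the null model", which "requires 60 preclinical AD cases (positive p-tau181) and 290 healthy ageing controls (negative p-tau181". From this the section concludes that 350 people form the development set and 150 the validation set (60 and 25 expected positives, 17% each). It closes by saying that a risk-of-bias tool (PROBAST) "confirms these development and validation strategies have a low risk of bias".
- The same section says that the biomarker combination defining positivity "is yet to be determined as the scientific literature is developing quickly".
- *Hand movement data collection* describes twelve tasks, "allowing for a number of finger-tapping measures to be calculated including, but not limited to, frequency, rhythm, inaccuracies". It adds that the range of tests is deliberately wide so that Aim 1 can show which ones combine best. *Speech-like data collection* adds eight recordings with several measures each. The Discussion describes "combining multiple tests to amplify the multivariable model input data [> 10,000 data points".
- *Statistical analysis*: penalised logistic regression is developed on 350 of 500 people, with cross-validated penalties, bootstrap for model uncertainty and a secondary deep-learning approach. Candidate models are assessed in the other 150, and the one with the highest AUC becomes TapTalk.

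**The concern.** The formula behind 60/290 takes two scores as given and asks whether their AUCs differ. TapTalk is not given: it is to be estimated in those same 350 people from a large, open list of measures. An AUC computed where a model was fitted is too high, so the 60/290 comparison is not one that can be made without bias on those people. The people who can give an unbiased comparison are the 150 held out, and they contain fewer than half of the positives that the section says are required.

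The closing sentence then presents the whole strategy as already appraised and cleared, although neither the outcome nor the predictors are fixed. A reader of the section would take the development sample as justified and its bias as checked. The choice of tasks for the smartphone test, and the algorithm used in Study 2.3, both follow from Aim 1.

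**Working it through.** **Inputs.** From *Sample size justification*: AUC 0.90 (the text says above 0.90) against 0.75; 60/290 for development; 150 with 25 positives, hence 125 negatives, for validation. Alpha, sidedness, power and the correlation r between the two AUCs are not given; a two-sided 5% test and r = 0 to 0.5 are assumed here.

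**Step 1: the plan's figure.** Hanley-McNeil variance, with Q1 = A/(2−A) and Q2 = 2A²/(1+A):

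Var(A) = [A(1−A) + (n₁−1)(Q1−A²) + (n₀−1)(Q2−A²)] / (n₁n₀)

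At n₁ = 60 and n₀ = 290, Var(0.90) = 0.000741 and Var(0.75) = 0.001473. With r = 0, the SE of the difference is √0.002214 = 0.0470. Then 0.15/0.0470 = 3.19, and power = Φ(3.19 − 1.96) = 89%. With the null variance in the alpha term, one-sided 5% and 90% power, the requirement is exactly 60 cases. So 60/290 reproduces as a comparison of two fixed, independent AUCs. No term depends on the number of measures or on fitting.

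**Step 2: how many measures.** This is a count from the task descriptions; the protocol does not print a total.

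- Hand series: 8 one-handed tasks plus 4 two-handed tasks × 2 hands = 16; × 2 (frequency, rhythm) = 32.
- Inaccuracies on the sequential tasks: 4. Motor reserve: 8. Bimanual cost: 8. Dual-task cost: 8. Hand total: 60.
- Speech: 8 recordings × 3 = 24, plus 4 to 12 motor-reserve ratios = 28 to 36.

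The total is 88 to 96, before covariates and deep-learned features. Positives per measure: 60/96 = 0.63 to 60/88 = 0.68.

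**Step 3: what fitting does.** Ridge and lasso logistic regression with cross-validated penalties were simulated at 60/290, with the best attainable AUC set at 0.90:

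| Scenario | AUC in the 350 | AUC in new people |
|---|---|---|
| 100 measures, ridge | 0.97–0.98 | 0.83 |
| 100 measures, lasso, 30 true signals | 0.96 | 0.82 |
| 100 measures, lasso, 10 true signals | 0.95 | 0.86 |
| 100 measures, lasso, 3 true signals | 0.94 | 0.88 |
| 50 measures, ridge or lasso | 0.94–0.95 | 0.85–0.88 |
| 20 measures, ridge or lasso | 0.92 | 0.88–0.89 |

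Other assumed correlations and sparsities gave results within 0.82 to 0.89 in new people. With 100 measures of pure noise, penalised ridge still showed 0.85 in the fitting data against a true 0.50.

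**Step 4: the held-out 150.** At 25/125, Var(0.90) = 0.001783 and Var(0.75) = 0.003537. The SE of the difference is √[0.001783 + 0.003537 − 2r√(0.001783 × 0.003537)].

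- r = 0: SE 0.0729, 0.15/0.0729 = 2.06, power 54%.
- r = 0.3: SE 0.0617, ratio 2.43, power 68%.
- r = 0.5: SE 0.0530, ratio 2.83, power 81%.

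By the same formula, at a true AUC of 0.85 power is 25%, 34% and 44%; at 0.88 it is 41%, 54% and 67%. With 25 positives, a sensitivity of 0.80 has a 95% half-width of 1.96 × √(0.80 × 0.20/25) = 0.157.

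**Step 5: the risk-of-bias sentence.** The tool's criteria are not in the documents and are not needed. The section leaves the definition of a positive open, and *Exclusion criterion* leaves it open whether cut-offs or continuous levels will be used. The measures are open-ended and the covariates optional. An appraisal made at this point cannot have covered the final outcome or predictors.

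**The case against.** Several points on the other side stand.

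- **The 0.90 is a planning alternative.** A reader might infer that an AUC above 0.90 is a property the plan promises and will miss. The documents do not support that. The shortfall in Step 3 also depends on fixing the ceiling at exactly 0.90. Ridge runs with a ceiling of 0.92 gave 0.89 to 0.91 in new people, and favourable lasso runs gave about 0.90; wording that says above 0.90 allows such a ceiling.
- **No power is stated.** A reader might infer that a declared power is missed. None is declared. Both scores come from the same people, and the model may include the null model's predictors, so positive correlation is likely. At 60/290 with r = 0.5, power is 80% at AUC 0.85 and 95% at 0.875. Even the held-out set would reach 94% at 0.90 if r were 0.7 (SE 0.0425, ratio 3.53).
- **Overfitting is addressed.** Penalisation, cross-validation, bootstrap and a held-out set are all planned, and the simulated loss with penalisation is 0.01 to 0.08. Positives per measure is not a direct gauge of a penalised model, and the protocol does not say that every countable measure will enter.
- **The 150 are described as testing cut-offs and sensitivity/specificity.** The section does not say that they must meet 60/290. That is true, but no other sample in the plan offers a comparison free of fitting optimism.
- **1,382 people are recruited.** A reader might extend the criticism to the Discussion's view that the dataset is large enough. That remark sits beside the 1,382 and is not challenged here. The analysis and sample size sections still fix 350 and 150.

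What remains is that 60/290 answers a different question from the one it is used for, and that the tool's confirmation is claimed too early.

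**Conclusion.** The concern holds as a fault in the written justification. The 60/290 figure is valid for two fixed scores and says nothing about how many people are needed to build one. In the 350, apparent AUC would be about 0.93 or higher for a model whose AUC in new people is roughly 0.82 to 0.89. That rests on a ceiling of 0.90, roughly 90 to 100 measures for the apparent figure, and the assumed sparsity and correlation. In the held-out 25/125, power at a true AUC of 0.90 is about 54% to 81% for r = 0 to 0.5 (Hanley-McNeil, two-sided 5%), and it is lower at any AUC reduced for optimism. If the winning model is also ranked in those 150, which the text leaves unclear, its AUC there would be somewhat flattering too.

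The statement that the tool confirms low risk of bias is unsupported on the section's own text. That does not show that the strategy has a high risk of bias, only that the claim cannot yet be made. Severity is minor to moderate: the design can stand, but the stated grounds for it cannot.

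**What to change.** In *Sample size justification*:

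1. Delete the sentence on the risk-of-bias tool, or say that the tool will be applied once the outcome and the candidate measures are fixed.
2. State that 60/290 sizes a comparison of two fixed scores and does not size model development.
3. State the alpha, sidedness, power and correlation that were assumed.
4. Give the power or precision of the held-out 25/125 at AUC 0.90 and at a lower AUC that allows for optimism, labelled as dependent on those assumptions.

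This costs a few sentences and no participants. The stated case for the sample becomes more modest.
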